## Abstract

**Background:**

This protocol describes the ‘development of outcome measures and suitable methodologies for dissemination and implementation approaches,’ a priority for implementation research. Although many evidence-based practices (EBPs) have been developed, large knowledge gaps remain regarding how to routinely move EBPs into usual care. The lack of understanding of ‘what it takes’ to install EBPs has costly public health consequences, including a lack of availability of the most beneficial services, wasted efforts and resources on failed implementation attempts, and the potential for engendering reluctance to try implementing new EBPs after failed attempts.

The Stages of Implementation Completion (SIC) is an eight-stage tool of implementation process and milestones, with stages spanning three implementation phases (pre-implementation, implementation, sustainability). Items delineate the date that a site completes implementation activities, yielding an assessment of duration (time to complete a stage), proportion (of stage activities completed), and a general measure of how far a site moved in the implementation process.

**Methods/Design:**

We propose to extend the SIC to EBPs operating in child service sectors (juvenile justice, schools, substance use, child welfare). Both successful and failed implementation attempts will be scrutinized using a mixed methods design. Stage costs will be measured and examined. Both retrospective data (from previous site implementation efforts) and prospective data (from newly adopting sites) will be analyzed. The influence of pre-implementation on implementation and sustainability outcomes will be examined (Aim 1). Mixed methods procedures will focus on increasing understanding of the process of implementation failure in an effort to determine if the SIC can provide early detection of sites that are unlikely to succeed (Aim 2). Study activities will include cost mapping of SIC stages and an examination of the relationship between implementation costs and implementation performance (Aim 3).

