## Methods

Although the primary aims of the described study are to determine if the SIC can be applied across EBPs from different service sectors and accurately predict successful implementation outcomes, data provided from this project will allow investigation of EBP-specific implementation outcomes. Analyses will include examination of the impact that site demographic characteristics have on implementation behavior and cost outcomes. Moreover, because of the stage independence of the SIC, the varying impact of behavior in different stages will be evaluated.

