#### Implementation performance: hypothesis testing

Replicating procedures from the original MTFC implementation trial, agglomerative hierarchical clustering methods will be employed to find similarities within sites from each of the EBPs with regard to both Proportion and Duration scores for each stage. Sites will be clustered using each of these variables independently, as well as together. Cox proportional hazard survival models will be conducted with days-to-event as a time to event outcome for each of the three sets of clusters. The events analyzed will include significant milestones such as program start-up and certification. Additional significant events will be determined in collaboration with EBP developers in order to ensure that the SIC is able to accurately predict milestones that are meaningful to the developers. It is hypothesized that each SIC version will produce outcomes similar to those found for MTFC such that both Proportion and Duration are significantly related to successful implementation outcomes [21]. The appropriate rate and necessary proportions might differ between EBPs and service sectors. Universal items will be evaluated to determine if they are more critical than unique items for successful implementation. For any analyses that combine retrospective with the prospective data, this characteristic will be included as a covariate to evaluate any differences.

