
#### Mixed methods analysis

Data from discontinued sites’ SIC assessment, as well as their site characteristics will be examined in relation to qualitative outcomes to help increase understanding of how site behavior, as defined on the SIC, relates to on-the-ground decision-making using the mixed method technique of ‘convergence’ [44, 46, 49]. This will allow for an assessment of the SIC’s utility in providing ‘early signal detection’ of potential problems impeding successful implementation (*e.g*., does longer duration in pre-implementation most often indicate that leadership does not have an accurate understanding of how to accomplish a key implementation activity?). Thus, qualitative data will help to inform if there are reliable patterns of behaviors that are linked to particular patterns of SIC scores, thereby helping to unpack the potential for SIC scores to serve as a proxy for less easily observed phenomenon.

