## Discussion

During the final year of study procedures for each EBP, developers will be collaboratively involved in determining the most beneficial uses of the SIC. All EBP-specific outcomes will be shared, and the way that the SIC operates for each EBP will be explained to the developers. For example, the original MTFC-SIC outcomes indicated that sites that linger too long in the pre-implementation phase are less likely to achieve successful program start-up; the EBP developers/researchers might use this information to inform future modifications to their implementation process such as developing an enhanced protocol for struggling sites. Similarly, the developers/purveyors might determine that such information is important feedback for sites as they decide if it is in their best interest to proceed or not. In order for the EBPs to benefit from the SIC, a full understanding of the scoring methods, interpretation, and potential utility must be conveyed.

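### Aim 2 asks whether the SIC can detect failing sites early, but the stated analyses measure association and explanation, not how accurately an early score pattern separates failures from successes

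*Protocol article*

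**What the plan says.** The abstract (Methods/Design) gives the purpose of Aim 2: "to determine if the SIC can provide early detection of sites that are unlikely to succeed (Aim 2"). The heading of Specific aim 2 repeats early detection as its subject. The first paragraph of Methods adds, as a primary aim, finding out whether the SIC can "accurately predict successful implementation outcomes".

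Two analyses bear on this.

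- Under Specific aim 1 (Implementation performance: hypothesis testing), "agglomerative hierarchical clustering methods will be employed to find similarities within sites from each of the EBPs". The clusters use Proportion and Duration scores, separately and together. Then "Cox proportional hazard survival models will be conducted with days-to-event as a time to event outcome for each of the three sets of clusters". The hypothesis is that "both Proportion and Duration are significantly related to successful implementation outcomes". On thresholds the section says only: "The appropriate rate and necessary proportions might differ between EBPs and service sectors".
- Under Specific aim 2 (Mixed methods analysis), "Data from discontinued sites’ SIC assessment, as well as their site characteristics will be examined in relation to qualitative outcomes", by the technique of convergence. The section says this will allow the SIC's usefulness for early signal detection to be assessed. It names no SIC data from successful sites, although Participants also recruits sites that reach competency.

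The Discussion says developers might treat the findings as "important feedback for sites as they decide if it is in their best interest to proceed or not".

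**The concern.** Early detection is a claim about classifying one site, at a time when its outcome is unknown. To support it, a study has to show how often sites with the warning pattern go on to fail, how often they succeed anyway, and how many failures lack the pattern. The named analyses give none of these.

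A Cox model on clusters compares groups. Agglomerative clusters are also defined relative to the other sites in the data set, so membership does not carry over to a new site without a further assignment rule. Convergence on discontinued sites can suggest why they failed, but cannot show how many successful sites had the same scores.

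At stake is what the result is taken to mean. If developers feed scores back to sites, they need to know the error rate of the signal, and a significant hazard ratio is not that figure.

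**Working it through.** The article gives no accuracy, power or sample-size figure for early detection, so there is none to reproduce. Its Power section covers only Rasch precision (±1 logit). Four checks follow.

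**1. Precision of the earlier hazard ratios.** SE(log HR) = |ln HR| / z.
- Start-up (Predictive ability of scores): HR 0.190, p = 0.01. SE = 1.661 / 2.576 = 0.645, so the 95% CI is about 0.05 to 0.67.
- Discontinuation (MTFC-SIC for real-world MTFC sites, 35 sites): HR 26.50, p < 0.002. Taking p = 0.002, SE = 1.06 and the CI is about 3.3 to 212. A smaller p would narrow it.

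**2. From hazard ratio to error rate.** Assume proportional hazards and two clusters. The documents do not give cluster sizes or start-up rates, so these are assumed. If a share p of fast-cluster sites starts up, the share of slow-cluster (flagged) sites that start up is 1 − (1 − p)^HR. At HR 0.19:
- p = 0.80: 1 − 0.20^0.19 = 1 − 0.737 = 0.263
- p = 0.60: 1 − 0.40^0.19 = 1 − 0.840 = 0.160

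With equal clusters and p = 0.80, sensitivity = 0.737 / (0.737 + 0.20) = 0.79 and specificity = 0.80 / (0.80 + 0.263) = 0.75. Varying the assumptions at the same HR of 0.19:

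| Share flagged | Start-up if not flagged | Flagged sites that still start | Sensitivity for no start-up | Start-ups wrongly flagged |
|---|---|---|---|---|
| 20% | 60% | 16% | 34% | 6% |
| 20% | 90% | 35% | 62% | 9% |
| 50% | 60% | 16% | 68% | 21% |
| 50% | 80% | 26% | 79% | 25% |
| 50% | 90% | 35% | 87% | 28% |

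One hazard ratio is thus compatible with sensitivity from 34% to 87%.

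The discontinuation result can look much better. If 10% of fast-cluster sites discontinue (assumed), HR 26.50 gives 1 − 0.90^26.5 = 0.94 in the slow cluster, so about 6% of flags are wrong. At the lower limit, HR 3.3, it gives 1 − 0.90^3.3 = 0.29, so about 71% are wrong.

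**3. Dependence of cluster labels on the sample.** In a simulation of 35 sites with two normally distributed scores, Ward linkage and two clusters (4,000 runs), one site's scores were held fixed and its 34 companions redrawn. Its label changed in 36% of runs when there were no real groups, and in 11% when there were two real groups 2 SD apart on each score. The data and linkage are assumptions; the article names neither linkage nor number of clusters.

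**4. Precision if accuracy were reported.** Participants (Specific aim 2) gives an estimate of eight discontinuations a year across EBPs. Exact (Clopper-Pearson) 95% intervals at an assumed sensitivity of 75%:
- 8 failures (6/8): 35-97%
- 16 failures (12/16): 48-93%
- 24 failures (18/24): 53-90%
- 32 failures (24/32): 57-89%

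The number of prospective years is an assumption. If failures are spread evenly over three EBPs, three years give 24 / 3 = 8 per EBP, so each EBP alone has an interval of about 35-97%.

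**The case against.** The strongest reply is that a condensed article may leave cut-points and accuracy measures to a fuller plan. That would answer a complaint about missing detail. It does not answer this one: the article says which analysis will assess early signal detection, and that analysis uses discontinued sites' SIC data only.

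Four stronger readings are tempting and should not be drawn.

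- *Early detection will be declared from a Cox hazard ratio.* The Cox models belong to Aim 1, where they suit the hypothesis of association. Aim 2 is largely exploratory: its qualitative output is a heuristic model for developing and testing hypotheses. No criterion for declaring success is stated.
- *The Cox test is the only quantitative link between scores and outcome.* Implementation performance and cost plans cost curves that bear on the optimal rate and Proportion for success. Measurement properties yields Rasch site estimates on a scale not tied to clusters. Prediction (Discussion) foresees using earlier scores to predict later milestones. None of these is described as giving classification accuracy.
- *A quarter to a half of flags would be wrong.* This needs 80% start-up in the fast cluster, equal clusters and, for the upper end (48%), an HR of 0.40. None of these stands in the documents, and it leaves out the HR of 26.50.
- *Sites that would have succeeded will be turned away.* The Discussion is conditional, leaves the decision with the site, and first mentions an enhanced protocol for struggling sites, where a false flag means extra support.

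Two further objections stand and limit the remedy. Retrospective sites are described as formerly implemented (minimum 15 per EBP), so they may include few failures. And since suitable rates and proportions may differ by EBP, a rule derived on MTFC may not transfer unchanged.

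**Conclusion.** The point holds as a mismatch between aim and analysis. Followed as written, the plan can show that SIC scores are associated with outcomes and can help explain failures. It cannot show how accurately an early-stage pattern separates sites that will fail from those that will succeed.

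The size cannot be fixed from the documents. At HR 0.19 with two equal clusters and proportional hazards, 16% to 26% of flagged sites would still start up, for assumed fast-cluster start-up of 60% to 80%. Other cluster sizes and start-up rates move sensitivity widely at the same hazard ratio. The conclusion itself does not rest on these figures; it follows from what the two analyses estimate.

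**What to change.** - Keep the cluster-based Cox models, labelled as the association analysis.
- Add an analysis of Stage 1-3 scores at a fixed landmark in prospective sites of both outcomes. Fix the rule beforehand from earlier data that include failures: MTFC, and retrospective sites where failures exist. Where a rule does not transfer between EBPs, use EBP-specific cut-points or internal cross-validation.
- Report sensitivity, specificity and predictive values with confidence intervals, pooled across EBPs, with EBP-specific results as descriptive.
- Include successful sites' SIC data in the convergence analysis; such sites are already among those recruited for interview.
- Word the early-detection conclusion as preliminary or hypothesis-generating, and do not rest it on a significant hazard ratio.

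The cost is analysis work on SIC data the study already plans to hold. The drawback is wide intervals at about eight discontinuations a year, which is itself a reason to show them.

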**Discussion:**

This project fills a gap in the field of implementation science by addressing the measurement gap between the implementation process and the associated costs. The goal of this project is to provide tools that will help increase the uptake of EBPs, thereby increasing the availability of services to youth and decreasing wasted resources from failed implementation efforts.

## Background

Although many evidence-based practices (EBPs) have been developed, large knowledge gaps remain regarding how to routinely move EBPs into usual care [1]. There is much still to be learned about the key processes necessary for successful implementation, including the steps that are essential to effectively transport EBPs into usual care, and how to measure if they have occurred well [2].

Efforts to examine implementation outcomes are hindered by the lack of standardized tools to measure the key processes and stages of implementation [3]. For example, no standardized method exists to measure or predict what early implementation activities are necessary for successful program start-up, or to estimate the costs and resources necessary to complete implementation over and above the cost of the EBP itself [4], limiting the accuracy of fiscal decision-making about total implementation costs. Such limitations impede the ability to develop interventions/strategies to enhance and support successful real-world implementation efforts.

With the increased focus and effort to implement EBPs in real-world community settings [5] comes recognition of the complexity of the task, which involves planning, training, quality assurance, and interactions among developers and system leaders, front line staff, and consumers [1]. It is generally thought that it takes a site a minimum of two years to complete the implementation process [6] and that achievement is strongly influenced by the success of the implementation methods [7]. However, little is known about which aspects of these methods are most important for successful implementation [8]. Recently, there has been increased focus on understanding what steps in the implementation process are essential to effectively transport EBPs [2,9].

There is consensus that implementation is likely a recursive process with well-defined stages that are not necessarily linear and that impact each other in complex ways [6,10]. A treatment developer or purveyor typically assists programs in navigating their way through each of the implementation stages in an effort to ensure that program elements are delivered in the manner intended. Researchers have called for the measurement of the key processes and stages of adopting an EBP, and the assessment of the fidelity of implementation methods [11,12]. As shown in Figure 1[11], implementation research includes three distinct levels of evaluation including patient, service, and implementation outcomes. Leading services researchers have noted the need for models, like that provided in Figure 1, to link key implementation stages and outcomes to service and patient outcomes [13,14]. To date, limited tools are available to inform distinctions between these key levels of outcomes, thus limiting the evaluation of these discrete processes.

**Figure 1 F1:**
[figure not shown]
**Conceptual model for implementation research (adapted from Proctor et al. **[3]**) Circled area shows target of proposal.**

The current protocol describes a study in which we seek to narrow this gap by focusing on further development of a measure (*i.e*., the Stages of Implementation Completion; SIC [15]). Through this study, we will examine the generalizability of the SIC across four EBPs in different service sectors serving child and family mental health needs. A glossary of terms is provided in the subsection below.

Glossary of terms used throughout the protocol

**Practice:** A given specific EBP.

**Site:** Newly adopting programs for each EBP.

**Phases:** Pre-Implementation, Implementation, and Sustainability.

**Stages:** The 8 Stages of Implementation on the SIC ranging from Engagement to Competency.

**Universal Items:** Implementation activities identified on the SIC that are common across the EBPs.

**Unique Items:** Implementation activities identified on the EBP-specific SIC that are unique to that EBP.

**Retrospective:** Data from sites that previously adopted the respective EBP prior to project.

**Prospective:** Data from sites that attempt to implement the EBP during the grant period.

### Considerations for measuring implementation

#### Progression and timing

Given the non-linear yet staged progression of implementation, the measurement of this process must be flexible enough to capture potential variations. Having a well-defined system of implementation and knowledge about the typical successful progression through the stages could increase the likelihood that a purveyor could provide sites with information in the early stages that will help to support their success in later stages [8] in order to help realistically assess and calibrate their efforts either to proceed, or reconsider whether or not their current implementation plan remains viable. Ideally, such a measure could indicate when agencies are starting to falter or are on an unsuccessful path. Determining when specific barriers hinder successful outcomes is crucial for understanding the implementation process. It would be useful to have early signals that such barriers are on the horizon, and to know what distinguishing factors make these barriers significant enough to prevent moving forward (*e.g*., site and/or fiscal considerations).

#### Learning from failures and success

Although organizational factors such as climate and culture have repeatedly demonstrated influence on successful implementation [16], less is known about when failures occur in the implementation process and what the site’s perceptions are as to why these failures occurred. Much can be learned from sites that initiate the implementation of an EBP and then fail to reach milestones such as start-up or sustainability [17] in addition to those that are successful. Until recently, studies recruited sites retrospectively [11] or used recruitment designs where EBP champions recruited sites to implement [7], therefore not reflecting real-world conditions in which sites often initiate the process. We propose a naturally occurring design in which sites self-select to adopt a practice. This allows for prospective observation of the specific barriers that are perceived by sites as insurmountable at particular stages in the implementation process, and the differences between sites that are and are not able to overcome them. We will evaluate if barriers that result in failure can be detected using a standardized measure.

#### Understanding the costs of implementation and when they accrue

Ritzwoller and colleagues [4] argued for the need for standardized methods of analysis of cost data for behavioral medicine implementation and suggested that this gap in knowledge might play a key role in why new interventions fail to translate from research to practice. Understanding cost is complex and difficult to estimate partly because such estimations depend on what phase of implementation the site is engaged in [3]. Related and important to communities, are the specific activities in the implementation process that are necessary (versus optional) for program success, and the resources required to complete them. Although leading theories and frameworks include conceptualization of implementation costs as an important factor (*e.g*., Figure 1), such costs are an understudied aspect of implementation science [18]. Using the SIC, we developed a standardized method for estimating implementation costs per stage that has the potential to generalize across EBPs and sites [19]. This could be of high value for decision-makers who are responsible for determining if they can afford to adopt new practices; some decision-makers might underestimate the resources needed for implementation, while others might over-estimate the needed resources and limit themselves from adopting practices that could be beneficial to their communities.

#### The Stages of Implementation Completion (SIC)

The SIC is an eight-stage assessment tool developed as part of a large-scale randomized implementation trial [15]. The trial contrasted two methods of implementing an EBP for youth with serious behavioral problems in the juvenile justice and child welfare systems, Multidimensional Treatment Foster Care (MTFC), in 53 sites in California and Ohio [20]. As shown in (Additional file 1), the SIC has eight stages with sub-activities within each stage. The stages range from Engagement with the developers to practitioner Competency and map onto three well-accepted phases of implementation (Pre-Implementation, Implementation, Sustainability) [2].

